##### Older adults

A specific questionnaire was also developed for community dwelling older adults to evaluate their perceived knowledge of their own health status, their awareness of lifestyle habits and modifiable risk factors, their understanding of community health resources and assets, and their overall satisfaction with the experience. This questionnaire will be completed at the end of the final session. Detailed questions are available in the supplementary file.

All items for both target populations will be rated on a 5-point Likert scale (1 = “not at all” to 5 = “very much”). All questionnaires will be created and administered through the REDCap platform. Research team members have undergone prior training to ensure their standardized administration and the accuracy of data collection.

In addition to the self-reported questionnaire, several validated instruments will be used to assess the health status of the older adults. The instruments include ICOPE tool to assess intrinsic capacity [16], the validated VIG-Frail scale to evaluate frailty status [41], the EuroQol-5D-5L to measure quality of life and eighteen indicators of NOC. The EuroQol-5D-5L is a widely used instrument validated for measuring self-perceived health and quality of life and has normative reference values for the Spanish population [42, 43].

The NOC was developed in 1991 at the University of Iowa following research involving professionals from various specialties, as a standardized grouping of outcomes obtained in nursing clinical practice. It enables the identification, naming, classification, and measurement of outcomes and indicators achievable through Nursing Interventions Classification (NIC), based on the profession’s own common Language [44]. The NOC is useful across all areas of nursing practice but can also be used by other healthcare professionals, as it describes the condition of patients, caregivers, families, or communities at a conceptual level and provides a classification of user outcomes that may be influenced by all healthcare disciplines [45]. Each NOC includes an identification number, a definition, and a set of indicators that describe specific states, perceptions, or behaviours related to the outcome, measured using a 5-point Likert scale (1 indicating severe and 5 indicating absence). The outcome helps healthcare professionals assess and quantify the condition of the patient, caregiver, family, or community [46]. The aim is to relate the nine priority conditions associated with the decline of intrinsic capacity according to ICOPE to nine NOCs, selecting two indicators for each NOC. In doing so, an added value will be provided to the ICOPE instrument, exploring the consistency and potential complementarity of both assessment approaches, as no study has yet been found that establishes this relationship. This innovative association between ICOPE and NOC aims to open new avenues for integrated assessment models in geriatric care, potentially improving the interdisciplinary understanding of functional decline. Exploring such correlations may also inform the development of shared care plans across professional domains.

As part of the qualitative data collection, focus groups will be conducted with all potential participants (students, professors, and older adults), who will be informed and invited to participate voluntarily at the end of each semester. Separate focus groups will be organised for students and professors, ensuring representation from the different undergraduate health degrees involved in the programme. These sessions will explore how they experienced their involvement in the Service‑Learning programme, whether it influenced their knowledge and competencies, and their perceptions of the programme’s value and areas for improvement. In parallel, focus groups will also be conducted with older adult participants to explore how the programme has affected their knowledge about their own health status, whether they have learned strategies to improve their health, and whether their awareness of community health resources has increased. All focus groups will be conducted online via Microsoft Teams, and sessions will be recorded to support accurate transcription. Details on the coding and thematic procedures for qualitative analysis are provided in the Statistical Analysis section.

### Statistical analysis

Descriptive statistics will be calculated for all study variables. Continuous variables will be summarised as mean and standard deviation for normally distributed data, or median and interquartile range for non-normally distributed data. Categorical variables will be expressed as absolute and relative frequencies (n, %). Normality will be assessed using the Kolmogorov–Smirnov test and visual inspection of histograms and Q–Q plots.

Mean scores for each dimension will be computed, and potential differences between degree programmes will be analysed using one-way ANOVA or Kruskal–Wallis tests, depending on data distribution.

A cluster analysis will be conducted to identify distinct student profiles based on their responses to the 29-item Service-Learning questionnaire covering the three dimensions of training, learning, and service. The K-means method will be applied, as it allows grouping students according to the similarity of their response patterns. Different values of *k* will initially be explored to determine the most meaningful and interpretable number of clusters. The final solution will be selected based on the internal coherence of the clusters and the clarity of their conceptual interpretation.

Once the final clusters are obtained, each group will be characterised by examining the mean scores of the questionnaire items or dimensions. This will allow the identification of distinctive patterns of perception and applicability of the Service-Learning methodology within each profile.

To examine how these profiles differ according to sociodemographic variables, subsequent analyses will be performed. Differences in age across clusters will be evaluated using ANOVA or the Kruskal–Wallis test when assumptions of normality and homogeneity of variances are not met. Associations between clusters and categorical variables such as sex and university degree will be assessed using chi-square tests.

A significance level of *p* < 0.05 will be applied to all statistical tests.

At baseline, univariate associations between ICOPE, VIG-Frail, and the components of the NOC outcomes will be explored. To examine linear relationships between continuous variables, Pearson’s correlation coefficients will be calculated when normality assumptions are met; otherwise, Spearman’s rank correlation coefficients will be used. Statistical significance will be set at *p* < 0.05. When multiple comparisons are performed, Bonferroni correction will be applied to adjust the significance threshold accordingly. No imputation methods will be applied for missing data, only complete-case analysis will be performed. The quantitative data will be analysed using SPSS software (version 29.0).

Qualitative data from focus groups will be conducted online via Teams. Participants will sign an authorization for recording and image use. The analysis process will be conducted by using a modified version of Colaizzi’s 7-stage method, which draws upon Husserl’s descriptive phenomenological approach that aims to describe the essence of lived experiences from the first-person perspective. In-depth thematic analysis will be finalized [47]. Adherence to the Standards for Reporting Qualitative Research will be ensured throughout the study [48].

A Data Monitoring Committee (DMC) has been established, consisting of the Principal Investigator, the study coordinator, one expert in data analysis, and one expert in the data collection platform (REDCap). The DMC will conduct periodic reviews of the intervention to ensure its adherence and data quality and analysis. Also, will monitor study progress and would be responsible for any decision regarding early termination if unforeseen circumstances arise.

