### Characteristics of participants or description of materials

The study comprises two population groups: university students and older adults. Students will be recruited from five undergraduate programs at UVic-UCC (Nursing, Physiotherapy, Human Nutrition and Dietetics, Occupational Therapy, and Psychology), specifically those enrolled in courses focused on ageing-related topics.

Participants aged 60 and above who can travel independently or with caregiver support to the UVic-UCC facilities will be eligible to participate. Individuals presenting cognitive impairment or significant communication difficulties will be excluded to ensure adequate understanding and participation in the intervention. Throughout the study, participants will remain under their usual care, since the intervention is designed to be compatible with and not a substitute for standard treatment. Recruitment will be through key associations and institutions in the Osona region. Snowball sampling and social media will also be used for participant enrolment.

The sampling performed is non-probabilistic and either consecutive or convenience-based, according to the criteria described above. The project will be presented at various community associations. Regarding the students, they will be recruited through the participating courses of the previously mentioned university degree programs.

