### Description of all processes, interventions, and comparisons

#### Structure of the intervention

The intervention will consist of three sessions, during which older adult participants will come to the university (Fig. 1). During the first visit, all older adults will meet at a designated meeting point with the professor, also the purpose and procedures of the intervention will be reviewed, and participants will be invited to participate in the study and asked to sign the informed consent form. Approximately 12–20 students will be present in the classroom, divided into groups of up to 5 students per each older adult as stated in Order SSI/81/2017 published in the Spanish Official State Gazette (BOE). A maximum ratio of five students per user is established in order to prevent an excessive number of students per participant, thereby ensuring the quality of learning and, most importantly, safeguarding the patient’s right to privacy and comfort [40].

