The next session will consist of a classroom-based student activity (without the older adults). During this session, students will prepare a report based on the CGA and will develop personalized health recommendations for the older adult, including health education strategies and suggestions for referral to appropriate community health assets and programs. The report will include: (1) a summary table of the common block results and key domains: frailty (VIG-Frail score), quality of life (EUROQOL-5D-5L), cognition, mobility, nutrition, vision, hearing, psychological status, social support, caregiver status, and urinary incontinence-interpreted based on the ICOPE and NOC responses; (2) a section on the (subject-depending) specific block, detailing the test used, its purpose, and results; and (3) a section with personalized health promotion and prevention recommendations, including community-based health resources aligned with the participant’s preferences and place of residence. All reports will be reviewed by the course professor and the project coordinator. This dual review process helps ensure the quality and consistency of the content before it is shared with the users.

The final session will include the visit from older adults. To improve adherence to the intervention plan, reminder phone calls will be made to participants before this session. During this visit, students will meet again at the university with the same older adults they assessed during the first visit and present the personalized health report prepared in class. The main objective of this session will be for students to explain their findings and recommendations, applying personalized recommendations to the specific case of the older adult. In cases where the participant is unable to attend the session in person, data collection will be conducted via telephone.

At the end of the intervention of each semester, focus groups with students, professors, and older adults will be conducted to explore their experiences and perceptions of the programme. Further details on the procedures and data collection methods for these focus groups are provided in the Data Collection Methods section.

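### Degree programmes are compared as if students were independent, although students share an older adult and a classroom, so the p-values for degree will be wrong, probably too small

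*Protocol article*

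**What the plan says.** For the three dimension scores of the Service-Learning questionnaire, the Statistical analysis section states that "potential differences between degree programmes will be analysed using one-way ANOVA", or by Kruskal–Wallis if the distribution calls for it. For the K-means student profiles it states: "Associations between clusters and categorical variables such as sex and university degree will be assessed using chi-square tests". A p-value threshold of "0.05 will be applied to all statistical tests". The section contains no random effect, cluster-robust variance or design effect.

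The delivery of the programme is described elsewhere in the article:

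- Characteristics of participants: "Students will be recruited from five undergraduate programs at UVic-UCC", and "they will be recruited through the participating courses of the previously mentioned university degree programs".
- Structure of the intervention: a classroom holds roughly 12–20 students, "divided into groups of up to 5 students per each older adult". The first session contains a block that depends on the subject taught. The course professor reviews the reports, along with the project coordinator. In the final session "students will meet again at the university with the same older adults they assessed during the first visit".
- Data collection methods, Students: the questionnaire is completed at the end of the third session, after all of this shared experience.

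**The concern.** The questionnaire asks students to judge an experience that they had together. Those who shared an older adult, a room and probably a professor are likely to answer more alike than students picked at random. ANOVA, Kruskal–Wallis and chi-square ignore that similarity. Choosing between ANOVA and Kruskal–Wallis by the shape of the distribution does not help, because both assume independent observations.

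What follows for the degree comparison depends on how classes are made up. If a class contains one degree only, variation between classes and teachers goes straight into the contrast between degrees, and p-values come out too small. A difference between two professors or two rooms could then be published as a difference between, say, nursing and psychology students. Profile by degree is a named student objective under Research aims, so such a result would be reported.

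**Working it through.** **Inputs from the article.** Five degrees; classes of 12–20; groups of up to five students per older adult; alpha 0.05; a provisional starting size of 304 (Power calculation). The article presents 304 as a figure from social-science literature, still to be adjusted, and gives no effect size, standard deviation, power or ICC. It cannot be rebuilt from the article's own inputs and serves here only as a scale.

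**Assumptions.** The ICC is not in the article, so a range is shown. The number of classes per degree is also not given. Single-degree classes are assumed first, then relaxed.

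**Step 1: hand calculation.** Take 5 degrees × 4 classes × 15 students = 300, in groups of five. With no true degree effect, the between-degree mean square is inflated by about

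DE = 1 + (15 − 1) × ICC(class) + (5 − 1) × ICC(group).

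With five degrees the F test behaves roughly like a chi-square on 4 degrees of freedom divided by 4, with 5% critical value 9.488. The true rejection rate is therefore about P(χ²₄ > 9.488/DE). For x = 9.488/DE this equals exp(−x/2)(1 + x/2).

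- Class ICC 0.01: DE = 1.14, x = 8.32, rate 8.0%.
- Class ICC 0.02: DE = 1.28, x = 7.41, rate 11.6%.
- Class ICC 0.05: DE = 1.70, x = 5.58, rate 23.3%.
- Group ICC 0.05 only: DE = 1.20, x = 7.91, rate 9.5%.

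**Step 2: simulation of the same layout** (normal scores, no degree effect, 3,000 replicates). For chi-square, three equal-sized categories of the score stand in for the profiles.

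| Assumed ICC | ANOVA | Kruskal–Wallis | Chi-square | Class means |
|---|---|---|---|---|
| none | 5.0% | 5.1% | 5.2% | 5.4% |
| class 0.01 | 8.6% | 8.4% | 7.0% | 4.7% |
| class 0.02 | 11.1% | 10.6% | 7.7% | 4.6% |
| class 0.05 | 24.2% | 22.4% | 14.5% | 5.2% |
| class 0.10 | 41.6% | 40.7% | 27.3% | 4.9% |
| group 0.05 only | 10.0% | 9.3% | 6.3% | 5.0% |
| class 0.05 + group 0.05 | 28.7% | 27.5% | 19.7% | 5.1% |

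Simulation and hand calculation agree. An ANOVA on class means keeps its 5% level throughout.

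**Step 3: 304 students.** With 19 classes of 16 (4, 4, 4, 4 and 3 per degree), ANOVA and Kruskal–Wallis reject about 7–8%, 12% and 24–26% at class ICC 0.01, 0.02 and 0.05. Chi-square rejects about 7%, 9% and 16%.

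**Step 4: one course per degree** (60 students each). ANOVA rejects 21.8% at ICC 0.01 and 68.1% at 0.05. Degree and teacher are then the same contrast, and no analysis can separate them.

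**Step 5: fully mixed groups** (one student from each degree around each older adult). The shared effect cancels from the degree contrast but stays in the error term. ANOVA rejects 3.8% at ICC 0.05 and 2.9% at 0.10, so the test is conservative.

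**Step 6: precision of overall means.** Effective size is 304/[1 + (m − 1) × ICC]. At ICC 0.05 this gives 304/1.20 = 253 for groups of five, 304/1.70 = 179 for classes of 15 and 304/1.95 = 156 for classes of 20.

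**The case against.** The strongest reply is that the article never says a class holds a single degree. It gives class size and group size, not composition. Interdisciplinary teamwork is a target skill under Research aims, and the limitations paragraph of the Discussion mentions multidisciplinary interaction among student groups. A reader might infer that classes and teachers are nested within degree as a matter of record, and that inflation is therefore certain. The text does not go that far: nesting rests on course-based recruitment, the subject-dependent block and the role of the course professor. This part of the objection stands, and the direction of the error has to be stated conditionally. It does not rescue the tests, because no mixed-degree allocation is described and full mixing would also make the p-values wrong.

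Second, the ICCs and the class layout are assumptions, and at the low end the excess is modest. That is right, as is the point that chi-square suffers less than ANOVA.

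Third, a reader might infer that the main student findings are invalid. They are not. The first student aim describes perceptions in three dimensions and involves no contrast between degrees; degree appears in the aims as one of three variables describing the profiles. Clustering alone does not bias the dimension means. It affects their precision and these secondary p-values.

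A full protocol or analysis plan might say more. But the article names the tests itself, so this is a stated method and not a detail left for later.

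**Conclusion.** The concern holds in conditional form. The named tests assume independent students, and the design described in the same article makes that assumption implausible. Nothing in the analysis, power or limitations text deals with it; the Bonferroni correction addresses multiplicity, not dependence.

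Under single-degree classes, the more natural reading, the true error of a nominal 5% test runs from about 7–8% to about 24–26% for ANOVA and Kruskal–Wallis, and from about 7% to 16% for chi-square, over class ICCs of 0.01 to 0.05. These figures rest on assumed ICCs, about 19 classes and 304 students. Under fully mixed groups the tests err the other way; partial mixing would fall in between. Only with negligible within-class and within-group correlation would the stated p-values be right.

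The plan should be corrected on this point, but the defect touches secondary comparisons and is not critical to the study.

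**What to change.** - **Identifiers.** Keep the class or course and the older-adult group for every student. Enrolment began before registration, so retrieve these from allocation records for students already enrolled. State whether classes and groups contain one degree or several.
- **Dimension scores.** Use a linear mixed model with degree as a fixed effect, random intercepts for class and for student group within class, and small-sample degrees of freedom (Kenward–Roger or Satterthwaite). An ANOVA on class means is a simple alternative when classes are single-degree.
- **Profile by degree.** Replace the chi-square p-value with a permutation test that reassigns whole classes to degrees.
- **Overall means.** Base their confidence intervals on the same clustering.
- **Few classes.** Where a degree contributes only one or two classes, report the degree comparison descriptively and do not attribute differences to the profession.

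The cost is analysis wording and, if they are not already held, two identifier fields and some retrieval work. The price is wider intervals and less favourable p-values. With few classes per degree, the class variance will be poorly estimated and some comparisons will have no usable test.

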### Users (≥ 60 years old)

Describe the characteristics of older adults including the prevalence of frailty and losses of intrinsic capacity.Identify the possible association between the ICOPE framework and VIG-Frail in individuals aged 60 and older.Investigate the possible association between the ICOPE and selected Nursing Outcomes Classification (NOC) indicators in individuals aged 60 and older.Analyse the impact of the program on their knowledge of their health status, lifestyle, risk factors of chronic conditions, community-based health assets and satisfaction.

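### The significance rules need reconciling, and the ICOPE–NOC tests should be confined to the 18 matched pairs the plan itself motivates, with methods suited to 5-point items

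*Protocol article*

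**What the plan says.** All of the text at issue is in the protocol article.

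- **Statistical analysis, end of the student analyses:** p < "0.05 will be applied to all statistical tests". No exception is given.
- **Statistical analysis, older-adult associations:** p < 0.05 is set again, followed by "When multiple comparisons are performed, Bonferroni correction will be applied to adjust the significance threshold accordingly". The set of tests that shares the correction is not named.
- **Statistical analysis, what is tested:** "univariate associations between ICOPE, VIG-Frail, and the components of the NOC outcomes will be explored". The method is introduced with "To examine linear relationships between continuous variables": Pearson if normality holds, otherwise Spearman.
- **Older adults (Data collection methods):** the instruments include "eighteen indicators of NOC". The stated purpose reads "relate the nine priority conditions associated with the decline of intrinsic capacity according to ICOPE to nine NOCs, selecting two indicators for each NOC". Each indicator is rated on a 5-point scale running from severe to absent.
- **Users (≥ 60 years old):** one aim is to "Investigate the possible association between the ICOPE and selected Nursing Outcomes Classification (NOC) indicators in individuals aged 60 and older", and another concerns ICOPE and VIG-Frail.
- **Power calculation:** 304 participants is a starting reference that will be adjusted. It is not divided between students and older adults.

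**The concern.** Three points meet in the same paragraphs.

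First, a blanket 0.05 and a conditional Bonferroni rule stand in one section without a sentence linking them. For the older-adult associations a reader can work out what is meant. For the student tests (degree comparisons, cluster profiles) a reader cannot tell whether the correction applies.

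Second, the rationale for the ICOPE–NOC work is narrow (each condition with its own NOC), while the analysis text is broad. Bonferroni charges every test in the family. Adding pairs for which the plan gives no rationale lowers the threshold for the pairs it does motivate. If the family is settled only after the data are seen, a result such as p = 0.001 is significant over 18 tests and not significant over 162.

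Third, the method does not fit the data. A single 5-point rating is ordinal, and ICOPE is described through conditions and losses, which are present or absent. A linear correlation for continuous variables is hard to interpret for such pairs. The chi-square, ANOVA and Kruskal–Wallis tests in the section are assigned to student analyses only.

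**Working it through.** **Inputs from the article.** Nine ICOPE conditions; nine NOCs with two indicators each, so 9 × 2 = 18 indicators, which agrees with the count in the Older adults section; nominal alpha 0.05. The article gives no number of tests, adjusted alpha, target correlation or older-adult sample size, so there is no stated figure to reproduce for this analysis.

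**Assumptions.** Two-sided tests. Fisher's z approximation, which is only approximate for Spearman and for ordinal or binary variables. n = 61 is one scenario: 304 read as students, at the maximum of five per older adult (304 / 5 = 60.8). n = 100 is a second scenario. n = 304 shows the case in which the reference figure applied to older adults.

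**Number of tests.**
- Matched pairs: 9 × 2 = 18.
- Full crossing of ICOPE with NOC, an upper bound for that block: 9 × 18 = 162.

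**Bonferroni threshold, alpha = 0.05 / m.**
- m = 18: 0.05 / 18 = 0.00278, two-sided critical z = 2.991.
- m = 162: 0.05 / 162 = 0.000309, critical z = 3.608.

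The ratio of the thresholds is 162 / 18 = 9.

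**Power = Φ(atanh(r) × √(n − 3) − z_crit).**
- n = 61, r = 0.5: 0.5493 × √58 = 4.183. For m = 18, Φ(4.183 − 2.991) = 0.88. For m = 162, Φ(4.183 − 3.608) = 0.72.
- n = 100, r = 0.3: 0.3095 × √97 = 3.048. For m = 18, Φ(3.048 − 2.991) = 0.52. For m = 162, Φ(3.048 − 3.608) = 0.29.
- n = 304, r = 0.3: 0.3095 × √301 = 5.370. For m = 18, power is 0.99; for m = 162, 0.96.

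**Correlation detectable with 80% power, r = tanh((z_crit + 0.842) / √(n − 3)).**

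| n | m = 18 | m = 162 |
|---|---|---|
| 61 | 0.465 | 0.526 |
| 100 | 0.371 | 0.423 |
| 304 | 0.217 | 0.251 |

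**Older adults needed for r = 0.3 at 80% power, n = ((z_crit + 0.842) / 0.3095)² + 3.** 157 for m = 18 and 210 for m = 162, an increase of 53, or about one third.

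**Cost of adding ICOPE total versus VIG-Frail (m = 19).** 0.05 / 19 = 0.00263, z = 3.008. Power is 0.88 in the first scenario and 0.52 in the second, and n for r = 0.3 becomes 158. The extra test costs almost nothing. Holm's first step uses this same threshold and its later steps are less strict, so these are lower limits for Holm.

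**The case against.** The strongest reply is that nothing here is really contradictory. The blanket sentence closes the student analyses, and the next paragraph gives the older-adult associations their own rule: nominal 0.05, corrected by Bonferroni. That reading is the natural one, and it stands. A reader might infer that these associations will be swamped by false positives, but that would require ignoring a correction the plan prescribes for exactly these tests.

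A reader might also infer that the associations will be undetectable. That does not hold either. Going from 18 to 162 tests moves the detectable correlation at n = 61 only from about 0.47 to 0.53. With 304 older adults, r of about 0.25 is detectable even over 162 tests. Since no older-adult sample size is fixed, no firm power conclusion is possible.

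The 162 tests are also not stated in the plan. The analysis text is compatible with the 18 matched pairs; it simply does not limit testing to them. Spearman is already the fallback, so a 5-point item would often be routed away from Pearson. A condensed article may leave the list of pairs and the divisor to a fuller document, and the absent divisor alone would not be a finding. The aims are worded as exploratory, and Bonferroni is valid.

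What remains is what the article does state: an unqualified 0.05 sentence beside an adjustment rule, analysis wording broader than its own rationale, and an association method framed for continuous variables when the NOC items are ordinal and ICOPE is described as conditions.

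**Conclusion.** The point holds as a minor-to-moderate defect of wording and analysis choice. The two significance sentences should be reconciled, and the plan should say whether the student tests are adjusted. The tested family should match the rationale. If it were allowed to grow to full crossing, the threshold would be nine times stricter. Power would drop by about 0.16 (r = 0.5, n = 61) or 0.23 (r = 0.3, n = 100), and about a third more older adults would be needed for r = 0.3. These figures rest on two-sided tests, Fisher's z and assumed sample sizes; at 304 older adults the loss for r = 0.3 is only 0.03. The mismatch between method and data type does not depend on sample size. Spearman covers score-to-score pairs adequately, but a condition that is present or absent against a 5-point item has no suitable method assigned. The exploratory status of the aims limits the consequence.

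**What to change.** In the Statistical analysis section:

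1. Qualify the blanket sentence: 0.05 is the nominal level and does not override the multiplicity adjustment. State whether the student tests are adjusted.
2. Define one tested family for the older-adult associations: the 18 matched ICOPE condition–NOC indicator pairs plus ICOPE total versus VIG-Frail, 19 tests in all. State how the ICOPE total is formed.
3. Replace Bonferroni with Holm, which controls the same error rate under the same conditions and is never less powerful.
4. Report all other pairs as estimates with 95% confidence intervals and no significance claim.
5. Use Spearman or Kendall for score-to-score pairs. For a condition present or absent against a 5-point NOC item, use a Mann–Whitney test with a rank-biserial effect or an ordinal logistic model. Do not use Pearson for NOC items.

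The cost is a few sentences and no extra data. The one drawback is that associations outside the matched pairs lose a significance label.

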### Power calculation

An initial sample size will be considered, and iterative calculations will be performed until adequate statistical power is achieved. As a reference point, we will start from the figure of 304 participants reported in the literature for studies in the field of social sciences [49]. However, since our research area differs substantially and is focused on health sciences, this initial value will be adjusted accordingly based on the specific characteristics and requirements of the study.

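### Optional improvement: Holm's step-down procedure could replace single-step Bonferroni for the older-adult associations, with the same 5% family-wise error and never fewer rejections

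*Protocol article*

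**What the plan says.** The older-adult part of the Statistical analysis section is framed as exploratory: "At baseline, univariate associations between ICOPE, VIG-Frail, and the components of the NOC outcomes will be explored". The statistic is a correlation coefficient: "Pearson’s correlation coefficients will be calculated when normality assumptions are met; otherwise, Spearman’s rank correlation coefficients will be used". The nominal level follows, "Statistical significance will be set at *p* < 0.05", and then the multiplicity rule, "When multiple comparisons are performed, Bonferroni correction will be applied to adjust the significance threshold accordingly". That rule is the ordinary single-step correction, in which each of m p-values is compared with 0.05/m.

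The likely number of tests has to be inferred from the Data collection methods, under Older adults: "The aim is to relate the nine priority conditions associated with the decline of intrinsic capacity according to ICOPE to nine NOCs, selecting two indicators". With a pair of indicators per outcome, that makes eighteen. The Power calculation section gives no effect size or target power for these associations. It offers only a provisional figure: "As a reference point, we will start from the figure of 304 participants reported in the literature for studies in the field of social sciences".

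**The concern.** Two of the four older-adult aims are associations, ICOPE with VIG-Frail and ICOPE with the NOC indicators, and the Discussion presents both as new. If these aims are read through which correlations pass a corrected threshold, the choice of correction affects how many true associations are declared.

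Single-step Bonferroni is dominated for that purpose. Holm uses the same p-values, needs no assumption about their dependence, holds the same family-wise error and can only add rejections. The article already accepts in its limitations that complete-case analysis may cost power, so a gain that needs no further data is worth considering. What is at stake is a modest amount of power, not the validity of any result.

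**Working it through.** **The plan's own figure.** The 304 is a borrowed starting value that the article says will be adjusted. It comes with no effect size, power or number of tests, so there is no power figure to reproduce.

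**Inputs.**
- From the article: level 0.05, Bonferroni, correlation tests, and nine conditions with two indicators each.
- Assumed: two-sided tests; m = 9 × 2 = 18 matched pairs; n = 61, 150 and 304; true r of 0.2 to 0.4. Only 304 stands in the article; 61 and 150 are illustrative.

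**Does Bonferroni do its job?** For m independent null tests the family-wise error is 1 − (1 − 0.05/m)^m. For m = 18 this is 1 − (1 − 0.00278)^18 = 4.88%, against 1 − 0.95^18 = 60% without correction. The rule works as intended.

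**Why Holm never rejects fewer.** Holm orders the p-values. With k hypotheses already rejected, it compares the next one with 0.05/(m − k). For m = 18 the thresholds run 0.05/18 = 0.00278, 0.05/17 = 0.00294, and so on, reaching 0.05/9 = 0.00556 after nine rejections and 0.05 for the last test. Every threshold is at least 0.05/18, so any p-value that passes Bonferroni passes Holm. In simulation this held in every run. The gain grows with the number of hypotheses already rejected, so it depends on how many associations are real.

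**Bonferroni power for one true association.** Power ≈ Φ(atanh(r)·√(n − 3) − z), with z = 2.991 for a two-sided level of 0.05/18. At n = 304 and r = 0.2: 0.2027 × 17.35 = 3.517; 3.517 − 2.991 = 0.526; Φ(0.526) = 70%.

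**Average power per true association, Bonferroni against Holm.** Simulated Fisher-z tests, independent, m = 18, at least 20,000 runs per setting, equal true r:

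| n, r | 9 of 18 real | 12 real | 15 real | all 18 real |
|---|---|---|---|---|
| 304, 0.2 | 70 vs 74% | 70 vs 77% | 70 vs 80% | 70 vs 86% |
| 150, 0.3 | 78 vs 82% | 78 vs 84% | 78 vs 87% | 78 vs 93% |
| 61, 0.4 | 59 vs 63% | 59 vs 65% | 59 vs 68% | 59 vs 74% |

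With one real association at n = 304 and r = 0.2 both give 69.8%. With three real in the settings of the table the gain is about 1 point. With test statistics correlated 0.3 and all 18 real, Holm gives 84%, 90% and 72% in the three rows, so the gain is slightly smaller.

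**Unequal strengths.** With true r spread evenly over 0.05 to 0.40:

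| n | 9 of 18 real | all 18 real |
|---|---|---|
| 61 | 19.1 vs 19.7% | 18.3 vs 19.5% |
| 150 | 46.1 vs 47.6% | 45.9 vs 50.1% |
| 304 | 63.8 vs 65.4% | 64.7 vs 70.2% |

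With nine real, 9 × 0.6 to 1.6 points is about 0.05 to 0.15 of one extra association found.

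**What hardly changes.** The chance of finding at least one true association differs by 0.1 point or less. At n = 304 and r = 0.30 both methods reach about 99% or more.

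**Actual family-wise error.** With half the tests null in the equal-r settings it is about 2.4% for Bonferroni and 3.5 to 4.4% for Holm.

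**The case against.** The strongest reply is that nothing here is wrong. Bonferroni is a standard, prespecified method that holds 5% under any dependence. It biases nothing, contradicts nothing in the article and breaks no stated power target. It also has properties that Holm lacks: one fixed threshold, a decision on each test that does not depend on the others, simple simultaneous intervals, and a bound of 0.05 on the expected number of false positives. A conservative rule for exploratory baseline correlations is a legitimate preference.

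Most of this stands, and it rules out three stronger readings that a reader might infer:

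- That real associations will be missed. Family size, sample size, strength and share of real associations are all left open, and the larger gains need every association to be real and equally strong. The indicators were chosen to match the ICOPE conditions, which makes many real associations plausible, but that is an inference and the article does not state it.
- That Bonferroni brings no benefit. It brings those listed above.
- That true associations would go unreported. The plan calculates a coefficient for the associations whatever the threshold, and nothing says that non-significant ones are withheld.

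What does not stand is the step from a legitimate choice to one not worth changing. The article calls for no simultaneous intervals and makes no use of a fixed threshold or of the bound on expected false positives. Once a 5% family-wise error is chosen, Holm uses that allowance more fully.

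**Conclusion.** The point holds as an optional, cheap improvement and not as a defect. Holm's dominance is a mathematical fact that does not depend on how the family is defined; the practical gain does. With 18 two-sided tests and n = 61 to 304, the gain in power per true association is:

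- about 0 to 1 point if few (one to three) are real;
- about 0.5 to 4 points if half are real;
- if all are real, about 1 to 5 points with unequal correlations and 12 to 16 points with equal ones.

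It is nil where a family holds one test, as it would if ICOPE with VIG-Frail were a single correlation in its own family, and close to nil where power is already near 100%. Leaving Bonferroni in place would make no result invalid.

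**What to change.** In the Statistical analysis section, replace the Bonferroni rule with wording such as: where several associations are tested together, the Holm step-down procedure will hold the family-wise error at 5%. The p-values are ordered; the smallest is compared with 0.05/m, the next with 0.05/(m − 1), and so on, stopping at the first that is not significant. Holm-adjusted p-values will be given beside every coefficient, significant or not.

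The cost is a change of one phrase and a sorted column of p-values, with no new data. Simple simultaneous confidence intervals and the single threshold are given up, and actual family-wise error rises slightly while staying within 5%. If the investigators want either of those properties, keeping Bonferroni and saying why is equally acceptable.
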